### Safety monitoring

If women raise any concerns about their health during recruitment and throughout the research process, they will be provided with numbers for counselling by the research team and they will be provided with appropriate referral to health care professionals to receive additional treatment and care.

PFME is currently part of antenatal and postnatal education and is considered a safe practice. There are no adverse effects previously reported in the literature; however, any adverse events arising during the study will be documented and reported to the Human Ethics Research Committee.

### Sample size

The sample size of this study was calculated based on the recent research available on the impact of PFME on SF in the postpartum period. Using information from this study [52], a total FSFI score of 28.9 ± 4.54 in the intervention group after PFME and 26.6 ± 4.40 in the control group and a standard deviation of 4.54 in both groups, a sample size of minimum of 62 in each arm would be required to detect a 9% difference in FSFI scores between groups (80% power and *α* = 0.50). The treatment and control ratio is 1. Allowing for 20% attrition during pregnancy, around 160 women are needed to be recruited. However, considering the possibility of a higher rate of withdrawal at 3 months after birth and anticipating 30% attrition after birth, 200 women will be randomised.

### Data management

Data will be collected via an electronic data management system (REDCap) and will be stored securely on a password-protected computer in the hospital setting. Data will be linked to a study code and de-identified data will be used for data analysis. All of the hardcopies will be de-identified using a study code and will be stored securely in the hospital setting. All data will be destroyed 5 years after completion of the study.

### Statistical analysis

Analysis of the primary and secondary outcomes will be based on an intention-to-treat basis, which will include withdrawal and losses to follow up. Descriptive statistics including numbers and proportions, and means and standard deviations will be used. Primary analysis including chi-square and Student’s *t* tests will be used to examine group differences in the primary and secondary outcomes. Repeated ANOVA will be used in order to assess within-patient correlation. Effect sizes will be reported with 95% confidence intervals, and results will be considered significant if *P* < 0.05. Data will be analysed using SPSS.

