### Eligibility criteria

Low-risk primiparous women who present to the antenatal clinic for antenatal care will be approached to participate in the study. Women will be eligible if they are primiparous, over 18 years old, ≤ 22 weeks’ gestation, have a singleton pregnancy, anticipating a vaginal birth and have no history of urinary incontinence, pelvic surgery or pelvic organ prolapse at baseline. They also should have no previous history of depression, mental illness, alcohol and drug use or domestic violence and they need to be able to read, understand and communicate in English. Participants in the treatment group must also agree not to perform a PFME programme other than that provided in this study. Women will be excluded if they are over 22 weeks’ gestation, planning to give birth via caesarean section at the time of booking, multiparous, have a multiple pregnancy, have complicated pregnancies (type 1 and type 2 diabetic, vaginal bleeding, baby with abnormalities, etc.) and have known pelvic floor muscle dysfunction. Women who are not able to read and understand English to answer the questionnaires will also be excluded from this study.

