Both study and control groups will receive routine antenatal care during pregnancy. The routine antenatal care includes verbal advice on PFME given by midwives to women at 28 weeks’ gestation. The advice is given in one antenatal visit and is known to be inconsistent and brief, as there is no structured PFME programme available. The available antenatal classes also do not cover a structured antenatal PFME training with follow up. The physiotherapy service is available to the women who are referred to a physiotherapist to receive specific physical therapy treatment.

In this study, women in the control group will not receive training on PFME from the researcher; however, they will not be discouraged from performing PFMEs. There is no dietary or lifestyle requirement or restriction as a result of participating in this study. Women in the intervention group are required to follow the PFME protocol provided by the researcher and to avoid using a different PFME protocol.

If women develop any complications related to pregnancy, they will be allowed to withdraw from the study if they are advised to do so by a doctor.

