To assess the compliance rate, women will be given a diary to record their PFME daily. These data will be collected and recorded monthly by the researcher.

All questionnaires are self-report questionnaires and will be delivered electronically through the REDCap electronic system [51] to women unless they choose to receive hardcopies. The first researcher ([name]) will collect the data. All missing data will be reported with reasons given and patterns of occurrence explored. If women withdraw from the study, no more additional information will be collected; however, the personal information already collected will be retained to ensure that the results of the research project can be measured properly and to comply with the law.

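### The protocol promises an intention-to-treat analysis that includes losses to follow-up, but the tests it names use only women with observed FSFI scores, so as written the result is an observed-case one

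*Protocol article*

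**What the plan says.** Under Statistical analysis, the article commits to analyses that "will be based on an intention-to-treat basis, which will include withdrawal and losses to follow up". It then names chi-square and Student's t tests as the primary analysis, which "will be used to examine group differences in the primary and secondary outcomes". It adds: "Repeated ANOVA will be used in order to assess within-patient correlation". The software is given as "Data will be analysed using SPSS".

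Under Outcome measures and data collection, FSFI is measured at booking (about 20 weeks), at 36 weeks and at 3 months after birth. The only statement on missing data is "All missing data will be reported with reasons given and patterns of occurrence explored". On withdrawal it says "If women withdraw from the study, no more additional information will be collected", while data already held are kept.

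Under Intervention used in this study, women who develop pregnancy complications are covered as follows: "they will be allowed to withdraw from the study if they are advised to do so by a doctor".

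Under Sample size, the plan allows for 20% attrition in pregnancy and anticipates 30% after birth, and sets the number randomised at 200.

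**The concern.** The promise and the named methods do not fit together. A woman without a 3-month FSFI cannot enter a t test of 3-month FSFI. A woman missing any one of the three scores is dropped from a standard repeated-measures ANOVA. The text that deals with missing data describes it but does not bring these women into the analysis. The article also gives the ANOVA the task of assessing within-patient correlation, which is not the treatment question. The trial needs the difference between arms at each follow-up visit.

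Two things are at stake. First, a published result would carry a label saying losses were included when the named methods leave them out. Second, losses may not be alike in the two arms. Only the intervention arm has a daily home programme of about 15 minutes, a diary and fortnightly text reminders, and the article itself says that compliance with such exercise remains a problem. Participants know their allocation and report the outcome themselves. If women with lower sexual function are more likely to leave the intervention arm, the women who remain will make the programme look better than it is.

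**Working it through.** **Step 1. Reproduce the plan's sample size.** Inputs from Sample size: means 28.9 and 26.6, SD 4.54, power 80%, ratio 1:1. The significance level of 0.05 is taken from Statistical analysis, and two-sided testing is assumed.

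- Difference: 28.9 − 26.6 = 2.3 points (2.3 / 26.6 = 8.6%, the stated 9%).
- n per arm = 2 × (1.960 + 0.842)² × 4.54² / 2.3² = 61.2, rounded up to 62. This matches the plan.
- The alpha of 0.50 printed in the Sample size section would give 18 per arm, so it reads as a misprint of 0.05. That is a separate matter and does not affect this point.

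**Step 2. How many women the named tests would use.**

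- Completers needed: 2 × 62 = 124.
- At 20% loss: 124 / 0.8 = 155 (plan: around 160).
- At 30% loss: 124 / 0.7 = 177.1, so 178 (plan: 200, rounded up).
- With 200 randomised and 30% lost: 200 × 0.7 = 140 observed at 3 months, 70 per arm. About 60 women have no 3-month score.
- Standard error at 70 per arm: 4.54 × √(2/70) = 0.767. Power = Φ(2.3 / 0.767 − 1.96) = Φ(1.04) ≈ 0.85.

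The inflation is built so that enough completers remain, which fits an observed-case analysis and not one that includes the losses. Power is adequate, so bias is the issue.

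**Step 3. Size of the possible bias, by simple arithmetic.** Assume control losses are random and a share m of the intervention arm is unobserved, scoring on average g points below the observed women. The observed intervention mean is then too high by m × g. With m = 0.30:

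| Gap g (points, assumed) | Bias | True difference if 2.3 is observed |
|---|---|---|
| 1 | 0.30 | 2.0 |
| 2.3 | 0.69 | 1.6 |
| 4.54 (1 SD) | 1.36 | 0.9 |

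**Step 4. The same question by simulation.** Assumptions: no true effect, SD 4.54, equal correlation between visits, and 30% loss in each arm. Loss is random in controls. In the intervention arm the log-odds of loss rise by b for each SD that the 36-week FSFI is lower. At visit correlation 0.6:

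| Slope b (assumed) | Observed-case bias (points) | Share of 2.3 |
|---|---|---|
| 0.25 | 0.20 | 9% |
| 0.5 | 0.39 | 17% |
| 0.7 | 0.52 | 23% |
| 1 | 0.69 | 30% |
| near-deterministic | 1.35 | 59% |

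Across correlations 0.4 to 0.7 and slopes 0.5 to 1.5, the bias runs from 0.27 to 1.02 points.

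**Step 5. What a better model does and does not repair.** In Step 4, adjusting for the booking and 36-week scores leaves at most about 0.03 points. That is because loss was made to depend on a score the model uses, and every woman was given a 36-week score. If loss depends instead on the 3-month score itself, the same adjustment leaves about 0.35 (slope 0.5) to 0.66 (slope 1). A sensitivity analysis is therefore part of the remedy.

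**The case against.** The strongest reply is that a t test can be run on multiply imputed data and would then include the losses. A condensed article may leave the imputation method to an analysis plan that is not shown. That stands as a possibility. The article does more than stay silent, however: it makes an explicit promise, names the methods, and describes missing data only as something to report and explore. Any fuller plan would have to repair what this text says.

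Several stronger readings are tempting but not supported:

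- **That the randomised comparison is lost.** Nothing moves women between arms or removes them for poor adherence. Observed women are compared as allocated, and the risk is attrition bias.
- **That stopping the exercises ends data collection.** The rule applies to withdrawal from the study, and adherence is tracked separately by diary. The article permits withdrawal after a complication on medical advice but does not require it. It does not address follow-up of women who only stop exercising.
- **That only 56% of women would remain.** This multiplies 0.8 by 0.7. The Sample size section reads as 30% in place of 20%; compounding would need 124 / 0.56 = 221.4, so 222 women, not 200.
- **That women are excluded from one arm after allocation.** Eligibility criteria says: "Participants in the treatment group must also agree not to perform a PFME programme other than that provided in this study". No text says a woman who refuses is removed or left out of the analysis. Asking every woman to avoid other programmes would conflict with the comparator, because controls receive routine exercise advice and are not discouraged from exercising.

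**Conclusion.** The point holds as a conflict between a stated promise and the methods stated to deliver it. As written, the 3-month FSFI result would rest on about 140 of 200 women at the anticipated attrition, under a label saying the losses were included. Power of about 0.85 is not the difficulty.

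The possible bias is roughly 0.2 to 1 point or more, about 9% to 43% of the 2.3-point target (0.2 / 2.3 and 1 / 2.3), and higher under extreme mechanisms. These figures rest on assumed dropout mechanisms, visit correlations and random loss among controls, none of which the article gives. They show what could happen and do not predict it. If loss is unrelated to FSFI in both arms, the bias is nil and only the mislabelling remains.

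**What to change.** - **FSFI analysis.** Replace the t test and repeated-measures ANOVA with a likelihood-based mixed model for repeated measures. In SPSS MIXED, use an unstructured covariance with arm, visit, arm-by-visit and booking-FSFI-by-visit terms, analyse women as randomised, and report the arm contrast at 3 months with its confidence interval. Multiple imputation that includes the booking and 36-week scores is an acceptable alternative. With booking FSFI as a covariate, a woman with no follow-up score adds no information to the model, so report how many there are and cover them in the sensitivity analysis.
- **Sensitivity analysis.** Add a missing-not-at-random analysis, for example shifting the unobserved intervention-arm scores down by the range of gaps in Step 3.
- **Follow-up wording.** State that women who only stop the exercises continue to receive the questionnaires and have their birth data extracted, and that collection ends only when a woman withdraws from follow-up.
- **Agreement on other exercise programmes.** If it is kept as an eligibility condition, seek it before randomisation and make it conditional on allocation to the intervention.

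If the authors prefer the named tests without imputation, they should describe the analysis as one of observed cases by allocated arm.

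The cost is small: analysis wording, the withdrawal text, and notice to the ethics committees and the registry. The scores needed are already scheduled, so no new visits follow. Recruitment began in February 2018, so the follow-up and agreement changes can only apply prospectively.

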**Fig. 3 Fig3:**
[figure not shown]
The schedual of enrollment, interventions and assessment

The secondary outcome endpoints will be examined as follows:Childbirth outcomes will include duration of the first, second and third stages of labour, fetal positions and presentation at birth; mode of birth; episiotomy and perineal trauma (1st, 2nd, 3rd and 4th degree perineal lacerations); and fetal outcomes including the APGAR score, head circumference, length and weight. Data regarding childbirth outcomes and fetal outcomes will be obtained from the hospital database after birth.Urinary incontinence symptoms and specific quality-of-life measures will be assessed using the short forms of the Urogenital Distress Inventory (UDI-6) [43] and the Incontinence Impact Questionnaire (IIQ-7) [43] at the time of booking at 20 weeks’ gestation, at 36 weeks’ gestation and also at 3 months following birth. The short forms of the UDI-6 and IIQ-7 are composed of six and seven questions, respectively. They are validated self-report questionnaires and have been shown to have a high degree of correlation with the longer forms of these questionnaires. Both questionnaires are recommended by the second international consultation on incontinence [44]. The UDI-6 is a six-item symptom inventory, specific to symptoms associated with lower urinary tract dysfunction, and combines information on stress, obstructive and discomfort symptoms. The IIQ-7 is a seven-item life-impact assessment instrument specific to UI, and covers separate domains of physical activity, travel, social/relationships and emotional health. Both measures were developed for self-administration and are intended to be used in combination. Women rate how much they experience impaired function of UI and the extent to which this UI affects their daily functioning with four response options per item (0 = “not at all”; 1 = “slightly”; 2 = “moderately”; 3 = “greatly”). For this study, we maintained the scoring procedure as described by the original developer: if more than two items are missing, a total score is not to be calculated. The mean score of items is multiplied by $$ 33\raisebox{1ex}{$1$}\!\left/ \!\raisebox{-1ex}{$3$}\right. $$ to convert to a 0–100 scale. Higher scores indicate more symptom distress (UDI-6) or more impact on daily life (IIQ-7) [45].Faecal incontinence (FI) symptoms will be assessed using a Waxner short form of faecal incontinence questionnaire [46] and has been validated in Australia [47]. The Waxner classification is a 20-point scale used to determine the severity of faecal incontinence and is widely used in Europe [46]. The Waxner questionnaire consists of five questions addressing solid, liquid, gas, changing underwear and lifestyle. Excellent or a score of 0 means continent to liquid and solid stool. Fair means incontinent to liquid and flatus. Poor or a score of 20 means total incontinence [46].

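### Perineal laceration degree is an ordered secondary outcome, but the only categorical test the plan names is chi-square, which in its ordinary form ignores the order of severity

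*Protocol article*

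**What the plan says.** Under Outcome measures and data collection, the secondary childbirth outcomes include "episiotomy and perineal trauma (1st, 2nd, 3rd and 4th degree perineal lacerations"), to be taken from the hospital database after birth. The degrees are a graded scale of severity. The protocol does not say whether women without a tear form a further level, whether degrees will be pooled, or where women delivered by caesarean section are counted.

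The Statistical analysis section covers all primary and secondary outcomes in one sentence: "Primary analysis including chi-square and Student’s *t* tests will be used to examine group differences in the primary and secondary outcomes". The only other inferential method is given as "Repeated ANOVA will be used in order to assess within-patient correlation", which cannot apply to something recorded once, at birth. The significance rule is "results will be considered significant if *P* < 0.05", and effect sizes with 95% confidence intervals are promised. No method for ordered categories is named, and no test is tied specifically to laceration degree.

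**The concern.** Pearson chi-square on a 2 × k table spends k − 1 degrees of freedom and gives the same result if the grades are shuffled. It asks whether the two distributions differ in any way, not whether one arm has milder or more severe tears. For a graded outcome the second question is usually the one of interest, and a test with one degree of freedom directed at it has more power when the shift is consistent across grades.

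The effect of the exercise programme on childbirth outcomes is a stated secondary objective. A real shift in severity could be reported as no difference because the test spread its power over patterns nobody was looking for. Nor does a multi-level chi-square supply a single directional estimate to go with the promised confidence intervals.

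**Working it through.** **The plan's own figure.** The only sample size stated is for the FSFI: 62 per arm, from means of 28.9 and 26.6 and "a standard deviation of 4.54 in both groups".

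- n = 2 × (1.960 + 0.842)² × (4.54 / 2.3)² = 2 × 7.849 × 3.896 = 61.2, so 62 per arm.
- This holds at two-sided 0.05 and 80% power. The α printed in that section is 0.50 and would give 18 per arm; that is a separate matter. Two-sided 0.05 is used below.
- Nothing is stated about power for laceration degree.

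**Number of women.** With 200 randomised 1:1 there are 100 per arm at most. The 20% attrition during pregnancy would leave 100 × 0.80 = 80 per arm at birth. Restricting to vaginal births would lower this by an amount the documents do not give. The range examined is 62 to 100 per arm.

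**Analytic check.** A one-degree-of-freedom test with 80% power at two-sided 0.05 has noncentrality (1.960 + 0.842)² = 7.849. Giving the same noncentrality to the unordered chi-square:

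| Levels | df | 5% critical value | Chi-square power | Loss (points) |
|---|---|---|---|---|
| 5 | 4 | 9.488 | 59.5% | 20.5 |
| 4 | 3 | 7.815 | 64.5% | 15.5 |
| 3 | 2 | 5.991 | 70.9% | 9.1 |

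**Simulation (20,000 trials per row).** Grades in the control arm follow an assumed distribution. The intervention arm is shifted by a common odds ratio (OR) at every cut-point: cumulative odds are multiplied by OR. For example, with control grades none/1st/2nd/3rd/4th of 25/25/40/8/2% and OR 2, the cumulative proportion without a tear goes from 0.25 (odds 1/3) to odds 2/3, or 0.40, and the proportion with at most a 1st-degree tear from 0.50 (odds 1) to odds 2, or 0.667. Pearson chi-square is compared with the Wilcoxon-Mann-Whitney test with ties. Differences were taken before rounding.

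| Assumed control grades | n per arm | OR | Chi-square | Wilcoxon | Difference (points) |
|---|---|---|---|---|---|
| Five levels, 25/25/40/8/2% | 62 | 2 | 34.1% | 56.0% | 21.9 |
| same | 70 | 1.5 | 14.3% | 26.4% | 12.1 |
| same | 70 | 2 | 38.6% | 60.4% | 21.8 |
| same | 100 | 2 | 54.9% | 76.3% | 21.3 |
| same | 100 | 3 | 94.0% | 98.8% | 4.9 |
| Four levels, 35/52/11/2% | 70 | 2 | 39.2% | 56.5% | 17.3 |
| same | 100 | 2 | 54.3% | 71.7% | 17.4 |
| Four equal levels | 100 | 3 | 95.9% | 98.9% | 3.0 |
| Three levels (none, 1st–2nd, 3rd–4th) | 70 | 2 | 42.9% | 53.6% | 10.7 |
| same | 100 | 3 | 94.9% | 97.5% | 2.7 |

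The linear trend test was within about 2.5 points of Wilcoxon throughout. A separate simulation of the four-level case gave losses of about 10 to 18 points.

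**Type I error.** With OR 1, chi-square rejected in about 4–5% of trials and Wilcoxon in about 5%.

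**The opposite case.** In one alternative where the difference did not run in a single direction across grades, the ordered test had about 6% power against 47% for chi-square at 70 per arm.

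**The case against.** The strongest reply is that the protocol never commits to the analysis criticised. The sentence begins "Primary analysis including chi-square and Student’s"; the word *including* leaves the list open. No test is assigned to laceration degree, and neither a trend version of chi-square nor pooling of degrees is excluded. This is a condensed article, the analysis plan is not shown, and item-level tests for secondary outcomes are commonly left to it. That limits how firmly the point can be put. It does not remove it, because the sentence does direct the secondary outcomes to chi-square and t tests, and a reader following it would reach for chi-square here.

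Three stronger readings are tempting and are not supported:

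- *The plan loses about 20 points of power.* That figure needs a fifth, no-tear level, an odds ratio near 2 to 2.5 and mid-range power. The documents fix none of these, and with other reasonable choices the loss is as small as about 3 points.
- *Sparse 3rd- and 4th-degree cells make chi-square untrustworthy.* In simulation it kept its type I error, so validity is not at issue.
- *Only 70 per arm will be available.* The 30% attrition in the Sample size section is tied to the period after birth, whereas laceration degree comes from the hospital database at birth.

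It is also fair to say that choosing chi-square for the P value does not prevent reporting a directional effect. And the ordered test is not better in every case: no direction for lacerations is stated, and the Background describes mixed evidence on labour outcomes.

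**Conclusion.** The point holds as a modest one. Laceration degree is ordered, the only categorical test named does not use the order, and against a consistent shift in severity that costs power. The size is about 5–22 points with five levels, about 3–18 with four and about 3–11 with three. This rests on assumed grade distributions, a proportional-odds shift with odds ratios of 1.5 to 3, 62–100 women per arm and two-sided 0.05. The weakness is one of efficiency and direction, not of false positives. It concerns a single secondary outcome for which no power is claimed, and the FSFI analysis is unaffected. It is a worthwhile improvement, not an error that must be corrected before the trial can proceed.

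**What to change.** Add one sentence to Statistical analysis. Laceration degree, among women with a vaginal birth (or with caesarean births handled by a stated rule), is compared between arms with the Wilcoxon-Mann-Whitney or linear-by-linear trend test and reported as a proportional-odds common odds ratio with its 95% confidence interval. The sentence should also fix the levels used, including where women without a tear are placed. Keep chi-square for binary or unordered outcomes such as episiotomy, mode of birth and fetal position.

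No new data are needed and the methods are standard. The statistical price is lower power against a non-monotone difference between arms. If analysis is restricted to vaginal births, the group is defined after randomisation and should be described as such. Settling this before the data are examined also removes a choice among codings and tests once results are known.

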### Outcome measures and data collection

The list of data collection instruments and time of data collection are presented in Table 3 and Fig. 3. The primary outcome of this study is the measurement of female SF during pregnancy and at 3 months postpartum which will be assessed using the Female Sexual Function Index (FSFI) [42]. The FSFI is a valid and reliable [42] multidimensional self-reported instrument for the assessment of female SF. It consists of 19 questions grouped into six domains: desire, arousal, lubrication, orgasm, satisfaction and pain. A value of 0–5 is attributed to each answer. The scores range from 2 to 36 and the lower the score, the worse the SF [42]. There are cut-off points to predict female sexual dysfunction. In 2006, Weig et al. [1] validated the FSFI in the USA and found that a cut-off score of 26.55 was enough to classify 70% of women with sexual dysfunction in the normal population. This score cannot be used for specific groups such as pregnant women, postpartum women, menopausal women and so forth [1]. SF will be assessed at 20 and 36 weeks’ gestation and at 3 months following birth.

**Table 3 Tab3:** Data collection instruments and time of data collection

	Collection time							
	Booking		36 weeks’ gestation		Birth		3 months after birth	
Data and tools	CG	IG	CG	IG	CG	IG	CG	IG
Primary outcomes								
SF (FSFI)	√	√	√	√	–	–	√	√
Secondary outcomes								
Urinary incontinence (UDI-6)	√	√	√	√	–	–	√	√
Faecal incontinence (FI questionnaire)	√	√	√	√	–	–	√	√
Specific quality of life (IIQ-7)	√	√	√	√	–	–	√	√
Childbirth outcomes (Obstetrix Database)	–	–	–	–	√	√	–	–
Confounding variables								
Depression (EPDS)	√	√	–	–	–	–	√	√
Relationship (RAS)	√	√	–	–	–	–	√	√
Expectancy questionnaire	√	√	–	–	–	–	–	–
Baseline data (Obstetrix Database)	√	√	–	–	–	–	–	–
Antenatal history (Obstetrix Database and survey)	√	√	√	√	–	–	–	–
Postpartum history (Obstetrix Database and survey)	–	–	–	–	–	–	√	√

*CG* control group, *IG* intervention group, *SF* sexual function, *FSFI* Female Sexual Function Index, *UDI-6* Urinary Distress Inventory, *FI* Waxner short form of faecal incontinence, *IIQ-7* Incontinence Impact Questionnaire, *EPDS* Edinburgh Depression Scale, *RAS* Relationship Assessment Scale

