
In order to examine the baseline characteristics that might interfere with the effect of PFME on SF, women in both control and intervention groups will be asked about depression symptoms (using the Edinburgh Postnatal Depression Scale (EPDS) questionnaire) [48]. The 10-question EPDS is a valuable and efficient way of identifying patients at risk for “perinatal” depression. Scores above 12 require further assessment and appropriate management as the likelihood of depression is high. Any woman who scores 1, 2 or 3 on item 10 requires further evaluation before leaving the office to ensure her own safety and that of her baby [48].

The other factor that can interfere with the effect of PFME on SF is the relationship with the partner. In this study, a relationship questionnaire [49] will be used at the time of enrolment and at 3 months following birth. The Relationship Assessment Scale (RAS) used in this study consists of seven questions. Scores could range from 1 (low satisfaction) to 5 (high satisfaction). The scores are added up and divided by 7 to get a mean score. The RAS is internally consistent and is solidly and consistently related to measures of relevant constructs such as love and self-esteem [49].

Women in the intervention group will also be provided with the expectancy questionnaire [50] at the time of enrolment. As there is no standard expectancy questionnaire available, for the purpose of this study a questionnaire was designed based on a questionnaire extracted from a study by Devilly and Borkovec [50]. This questionnaire will provide information on women’s expectation of treatment. Belief usually has two aspects to it: (1) what one thinks will happen; and (2) what one feels will happen. The original questionnaire has demonstrated high internal consistency within each factor and good test–retest reliability [50].

Data to be collected from the woman at baseline include: age, gestational age, education, economic status, country of birth, relationship status, smoking habits, remedies or medication history, medical, surgical and psychological history (such as mental illness or depression), family history including domestic violence and alcohol and drug abuse. Antenatal, birth and postpartum history will be obtained from the hospital database and a self-designed survey. The survey will be completed at the time that questionnaires are given to women at the time of booking, at 36 weeks’ gestation, and at 3 months after birth.

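### The primary FSFI comparison is an unadjusted t test although booking FSFI is collected in both arms: a valid test, but one that gives up precision

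*Protocol article*

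**What the plan says.** The Statistical analysis section of the protocol article describes the primary analysis as including chi-square and Student's t tests, which "tests will be used to examine group differences in the primary and secondary outcomes". It mentions no covariate, change score or baseline term. It then adds: "Repeated ANOVA will be used in order to assess within-patient correlation". Effect sizes are to be reported with 95% confidence intervals, and significance is judged at P < 0.05.

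Under Outcome measures and data collection, the primary outcome is defined: "The primary outcome of this study is the measurement of female SF during pregnancy and at 3 months postpartum". The timing is also given: "SF will be assessed at 20 and 36 weeks’ gestation and at 3 months following birth". Table 3 ticks FSFI at booking for both control and intervention groups. It does the same for the urinary (UDI-6), incontinence-impact (IIQ-7) and faecal incontinence scores.

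Table 3 places the depression scale (EPDS) and relationship scale (RAS), at booking and at 3 months, under the heading "Confounding variables". The text explains the depression measure as collected "In order to examine the baseline characteristics that might interfere with the effect of PFME on SF" and describes the relationship with the partner as another such factor. The Statistical analysis section does not mention either scale.

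The Sample size section starts from the means and SDs of an earlier postpartum study, 28.9 ± 4.54 with the exercise and 26.6 ± 4.40 without. For the calculation it takes "a standard deviation of 4.54 in both groups". These are SDs of the score itself, not of a change or a residual, which fits an unadjusted two-group comparison.

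**The concern.** A woman's FSFI score before the exercise programme is likely to predict her score afterwards. A t test on follow-up scores leaves that predictable variation in the error term. A linear model with the booking score as covariate (ANCOVA) removes it, for one degree of freedom and no extra data.

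Two consequences follow from the same source. On average over randomisations, the confidence interval is wider than it needs to be. In the one sample actually obtained, any chance difference between the arms in booking FSFI passes in part into the estimated effect. The Randomisation and blinding section mentions no stratification on FSFI that would limit such a difference.

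This is a matter of what the article states, not of detail left to another document: it names its primary test. The choice should be settled before results are seen by arm, because adjustment decided afterwards is open to challenge.

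**Working it through.** **Inputs**
- Target difference: 28.9 − 26.6 = 2.3 FSFI points (Sample size section); 2.3/26.6 = 8.6%, which the protocol gives as 9%.
- SD 4.54 in both arms, power 80%, 1:1 allocation (Sample size section).
- Two-sided α = 0.05. The threshold comes from the Statistical analysis section. Sidedness is not stated. The Sample size section prints α as 0.50, which would give 18 per arm two-sided, so it cannot be the value used.
- 70 evaluable women per arm: 200 randomised less the anticipated 30% = 140.
- Correlation r between booking and follow-up FSFI: not given. Assumed 0.3, 0.5 and 0.7.

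**Step 1. Reproduce the plan's figure.** n per arm = 2 × SD² × (1.96 + 0.84)² / 2.3² = 2 × 4.54² × 7.85 / 5.29 ≈ 61.2, rounded up to 62. The t-based solution is 62.1. The stated minimum of 62 per arm is therefore that of an unadjusted two-sample comparison.

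**Step 2. Power of the planned test at 70 per arm.** Standardised difference d = 2.3/4.54 = 0.507. The two-sample t test has power 84.5%.

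**Step 3. Power with booking FSFI as covariate.** The residual SD is 4.54 × √(1 − r²), the variance falls by r², and the standardised difference becomes 0.507/√(1 − r²). The standard error (SE) is residual SD × √(2/70).

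| r (assumed) | Residual SD | Variance reduction | SE of difference | Power, 70 per arm | n per arm for 80% power |
|---|---|---|---|---|---|
| unadjusted | 4.54 | 0 | 0.767 | 84.5% | 62 |
| 0.3 | 4.33 | 9% | 0.732 | 87.7% | 56 |
| 0.5 | 3.93 | 25% | 0.665 | 93.0% | 46 |
| 0.7 | 3.24 | 49% | 0.548 | 98.6% | 32 |

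The powers use the t distribution. The normal approximation gives 85.0%, 88.1%, 93.3% and 98.7%. The sample sizes in the last column use the normal approximation. For weaker correlations the step-3 formula gives 84.9% at r = 0.1 and 85.9% at r = 0.2.

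**Step 4. Chance imbalance.** Assume that booking FSFI also has SD 4.54. The protocol gives that SD only for scores after the exercise programme. The booking difference between arms then has SE 4.54 × √(2/70) = 0.767, with 95% limits of 1.96 × 0.767 = ±1.50 points. With equal SDs at the two times, the regression slope of follow-up on booking is r, so the shift in the unadjusted estimate is r × 1.50:
- r = 0.3: 0.45 points, 20% of 2.3
- r = 0.5: 0.75 points, 33% of 2.3
- r = 0.7: 1.05 points, 46% of 2.3

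**The case against.** **The t test is valid.** Under randomisation it is unbiased and keeps its type I error, and its standard error already allows for chance imbalance. Steps 3 and 4 therefore describe largely one loss seen from two sides. The trial is also sized for the test it names. All of this stands. A reader might infer that the result would be biased or the trial underpowered; the figures support neither.

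**Repeated ANOVA may use booking FSFI.** It could, if booking is one of its time points, so it would go too far to say that the plan makes no use of the baseline. But the text gives it the purpose of examining within-patient correlation and does not call it primary. If booking were included, its main effect of group would average in a pre-treatment score. The word including also leaves the list of primary tests open, yet no baseline-adjusted estimate is named anywhere.

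**The gain is uncertain.** Birth and most of a year of physiological change separate booking from 3 months postpartum, so r may be low. This stands: at r = 0.3 the gain is about 3 percentage points of power, and below that it is smaller still.

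**The imbalance can be overstated.** A reader might set the full 1.5-point booking difference against the 2.3-point target and read 65%. Only r times that difference reaches the estimate, so the supportable range is 20% to 46% at the 95% limit.

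**EPDS and RAS.** The heading in Table 3 covers their 3-month values, and a reader might infer that the trial will adjust for measurements taken after randomisation. No section plans this, and the text under Outcome measures speaks of baseline characteristics. That they have no stated role in the analysis is a matter of covariate detail that an article may leave to the full plan.

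**Urinary scores.** Women with a history of urinary incontinence are excluded, so booking UDI-6 and IIQ-7 may vary little and adjustment may gain little. This stands.

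**Conclusion.** The point holds as one of efficiency. The protocol names an unadjusted t test as its primary FSFI comparison while collecting booking FSFI in both arms, and the repeated ANOVA does not supply a baseline-adjusted primary estimate. At 70 per arm, adjustment would cut the variance by 9% to 49% and raise power from about 84.5% to between 87.7% and 98.6%. It would also remove a possible shift of about 0.45 to 1.05 points from a booking difference at its 95% limit. These sizes rest on an assumed r of 0.3 to 0.7, and the shift also on an assumed booking SD of 4.54. The change should be made because it is almost free, not because the planned test is wrong.

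**What to change.** State that the primary analysis is a linear model of follow-up FSFI total on arm with booking FSFI as covariate, and report the adjusted mean difference with its 95% confidence interval. Treat UDI-6, IIQ-7 and the faecal incontinence score in the same way, each adjusted for its own booking value; the gain for the two urinary measures may be small. The unadjusted t test can remain as a supporting analysis. If EPDS or RAS are used as covariates, say that only their booking values will be used, since the 3-month values are measured after randomisation.

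The cost is a change of wording before results are seen by arm. The model can be fitted in SPSS with data already scheduled in Table 3, and the sample size need not change.
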